#### Gender-Specific Analyses

We will undertake a planned subgroup analysis for the primary outcome measure, separately for women and men.

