## Methods and Analysis

### Study Design

The intervention will be evaluated in a multicentre, single-blinded randomized controlled parallel group design, in seven European countries. Within each participating country, one trial centre will lead the recruitment. Participants will be randomized in a 1:1 ratio to either the intervention or the control group, who will receive care as usual. The intervention will be delivered during the first 6 months after randomisation. Assessments will be performed at baseline (t0), at the end of the intervention phase, that is, after 6 months (t1), and after 12 months (t2) for follow-up (see Figure 1).

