### Sample Size Calculation

We assume that 5% of the target population will have documented ACP wishes at baseline. The study is powered to show a 20% absolute increase from a baseline of 5% (control group) in the primary outcome measure, that is, documented ACP-decisions, at 6 months, with a power of 0.80, a statistical significance of 0.05 (two sided) and an intraclass correlation coefficient (correcting for clustering within countries) of 0.10, by a Fisher's exact test. With the above assumptions, 74 patients in each treatment group are required. The sample size will be increased to 93 patients in each treatment group for allowing a 25% dropout rate within the 6-month follow-up period for the primary outcome effectiveness evaluation.

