### Statistical Analysis

#### Primary Endpoint

To evaluate the effectiveness of the intervention, all analyses of endpoints will be done in the intent-to-treat population. The primary efficacy analysis will be to investigate the effect of the PD_Pal intervention on the percentage of patients with documented ACP decisions from baseline to month 6 in the intervention and care-as-usual group. This will be tested by means of the Mantel Haenszel estimate method and by using multilevel logistic regression model, with data clustered within countries and with categorical factors (groups) and baseline characteristics as covariates, in order to test which independent variables (indicators) contribute to the effect of the intervention. The primary analysis will be repeated for the t2 assessment (12 months after randomisation) and also using the per-protocol population to confirm the overall study results. All tests will be performed two-sided, and *P*-values < 0.05 will be considered statistically significant.

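### The planned analysis by sex is run separately in women and in men with no sex-by-treatment comparison named, so it cannot show whether the effect differs by sex and will often produce a misleading split result

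*Protocol article*

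**What the plan says.** The section Gender-Specific Analyses is a single sentence: "We will undertake a planned subgroup analysis for the primary outcome measure, separately for women and men".

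The primary-endpoint part of Statistical Analysis names a Mantel-Haenszel method and a multilevel logistic model with countries as clusters. It then sets a rule for everything that follows: "All tests will be performed two-sided", with P < 0.05 as the threshold. The Bonferroni adjustment under Secondary Endpoints covers the secondary outcome measures only.

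The trial is sized as a whole: "The study is powered to show a 20% absolute increase from a baseline of 5% (control group) in the primary outcome measure", at 80% power. It states that "74 patients in each treatment group are required", and then: "The sample size will be increased to 93 patients in each treatment group for allowing a 25% dropout rate".

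The article names no interaction between sex and treatment, no estimate of the difference between the sexes, and no rule for reading the two results together.

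**The concern.** The question behind a subgroup analysis by sex is whether the effect differs between women and men. Running the primary comparison once in each sex answers a different question, twice: is there an effect in women, and is there an effect in men? A significant result in one and a non-significant result in the other does not show that the effects differ.

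The trial has 80% power only as a whole, so each sex alone has less information. An identical true effect can easily give P < 0.05 in one sex and not in the other. This is the only subgroup analysis the article names, so its result will carry weight. If it showed an effect in men but not in women, or the reverse, it could influence who is offered advance care planning support. The primary conclusion of the trial is not affected.

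**Working it through.** **Inputs**

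- From Sample Size Calculation: 5% v 25% documented decisions, two-sided 0.05, 74 evaluable per arm, 93 randomised per arm, 25% dropout.
- From Study Design: 1:1 allocation.
- Assumed: 35-50% women, because the article gives no sex split; equal split of each sex between arms; the same true effect in both sexes.

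**The plan's own figures**

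- For 5% v 25%, 80% power and no clustering, the pooled z formula gives 49 per arm and exact Fisher gives 55 (power 0.801). So 74 does not follow from the two proportions alone. The text also gives an "intraclass correlation coefficient (correcting for clustering within countries) of 0.10" but not how it was applied. That is a separate matter; here 74 is used only as the planned evaluable number.
- 93 is 74 × 1.25 = 92.5, rounded up. After 25% loss, 93 × 0.75 = 69.75, so about 70 per arm remain.
- Expected events over both arms: 70 × (0.05 + 0.25) = 21; 74 × 0.30 = 22.2.

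**Chance that exactly one sex is significant**

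With power Pw in women and Pm in men, the chance is Pw(1 − Pm) + Pm(1 − Pw). Power is obtained by enumerating all outcomes of two binomials. The uncorrected chi-square is the closer stand-in for the planned Mantel-Haenszel analysis. Fisher's exact test appears in the article only for the sample size.

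| Women/men per arm | Chi-square power, women/men | Exactly one significant, chi-square | Exactly one significant, Fisher |
|---|---|---|---|
| 24/46 (70) | 0.535/0.822 | 0.478 | 0.546 |
| 28/42 (70) | 0.601/0.784 | 0.443 | 0.541 |
| 35/35 (70) | 0.703/0.703 | 0.418 | 0.495 |
| 26/48 (74) | 0.575/0.839 | 0.449 | 0.546 |
| 30/44 (74) | 0.633/0.804 | 0.419 | 0.525 |
| 37/37 (74) | 0.728/0.728 | 0.396 | 0.484 |
| 37/56 (93, no dropout) | 0.728/0.880 | 0.327 | 0.444 |
| 46/47 (93, no dropout) | 0.822/0.831 | 0.287 | 0.408 |

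Worked example, 28/42: 0.601 × 0.216 + 0.784 × 0.399 = 0.130 + 0.313 = 0.443. The split falls mostly against the smaller group: men alone 0.313, women alone 0.130.

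**Comparison with an interaction test**

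In simulated trials with the same true effect in both sexes, a sex-by-treatment test at nominal 0.05 was significant in about 1.0-1.5% of trials on the log-odds scale (conservative at these counts) and about 5.5-6% on the risk-difference scale.

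**No effect in either sex**

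For a test of exact size 0.05, one-sex-only significance has probability 2 × 0.05 × 0.95 = 0.095. With 5% in both arms the real tests fall below this: about 7-8% for the uncorrected chi-square and 0.5-1% for Fisher.

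**Clustering**

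The table ignores it. A variance inflation of about 1.3, in the normal approximation, lowers power in each sex and gives 0.49-0.51 at 70-74 per arm with 40-50% women. Ignoring clustering therefore does not exaggerate the problem at those sizes.

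**Precision of the interaction**

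With 35 per arm per sex, expected events are 1.75 and 8.75. The variance of one log odds ratio is about 1/1.75 + 1/33.25 + 1/8.75 + 1/26.25 = 0.754. For the difference between the sexes it is 1.508, standard error 1.23. A 95% CI for the ratio of odds ratios then runs from about one-eleventh to eleven times the estimate (exp(1.96 × 1.228) ≈ 11).

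**The case against.** **The analysis plan may add an interaction test.** The article is a condensed protocol, and reporting results by sex is compatible with also fitting an interaction. This limits the point: the absence of an interaction test is not itself a finding. What stands is that the article states a method, separate analyses, alongside a general P < 0.05 rule. That method does not answer the question, and nothing else in the text compares the sexes.

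**The primary model may already look at effect modification.** It uses baseline characteristics as covariates and is said to test which variables contribute to the intervention's effect. But the text names neither sex nor an interaction, and a covariate main effect does not test effect modification. This does not rescue the plan, though it shows where the fix belongs.

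**Fisher's test overstates the size.** It is conservative at these counts and is not the planned analysis. This stands, so the headline is the 40-48% range, with about 48-55% for Fisher at 70-74 per arm as a side figure. The outcome comes from chart review, so some dropouts may still be evaluable, which would move the chance toward the 29-33% seen at 93 per arm.

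**A stronger reading is tempting.** A reader might infer that the trial has a high chance of falsely claiming benefit in one sex only. The article does not support that. It never says the two results will be contrasted, and two differing P-values are not in themselves a claim.

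**Conclusion.** The point holds as a poorly chosen stated method, not as missing detail. Separate within-sex analyses judged at P < 0.05 cannot show whether the effect differs by sex.

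If the intervention works equally in both sexes as designed, exactly one sex is significant in about 40-48% of trials at 70-74 evaluable per arm. At 93 per arm without dropout and with 40-50% women, it is about 29-33%. An interaction test would signal a difference falsely in about 1-6%.

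These figures rest on the full 20-point effect, an assumed 35-50% women, an uncorrected Mantel-Haenszel-type test and no clustering. With no effect in either sex the figure is at most about 9.5%. They measure how often a misleading pattern appears, not how often it would be misreported. The change is worth making because it is cheap and concerns the one subgroup analysis named in advance.

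**What to change.** Replace the sentence under Gender-Specific Analyses with wording such as: *Effect modification by sex will be assessed by a treatment-by-sex interaction in the primary multilevel logistic model, reported with a 95% confidence interval and labelled exploratory. Sex-specific effect estimates with 95% confidence intervals will be shown descriptively, without separate significance tests. A non-significant interaction will not be interpreted as evidence of equal effects.*

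Keep the interaction within the planned model. A difference between country-stratified estimates would spread about 21 events over 7 × 2 × 2 = 28 cells of about 140/28 = 5 patients each.

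The cost is one paragraph and no new data. The drawback is imprecision: the interval will be very wide. A control group of 24 women has probability 0.95^24 = 0.29 of no events at all, so the analysis plan should name a fallback, such as a penalised likelihood, for an empty cell.

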#### Other Study Parameters

Information regarding perceived care coordination and feasibility of the intervention will be obtained in optional qualitative interviews. To assure the quality of this multicentre, multinational, multi-language qualitative study, we will build on the lessons learned from the CLaSP trial (62), in which many of the study centres participated, and on recommendations and experiences described in the literature (63).

Software for qualitative analysis will facilitate data storage, coding, searching both within and across sites, and participant groups, retrieving data and recording analytical thinking (e.g., NVivo or AtlasTi). The data are linked with the quantitative data to interpret the change in patients/FCs of the quantitative outcome measures, their clinical significance, and the impact of the intervention at two levels (people and context; processes and tasks), and to identify ways to enhance the intervention and the processes for wider implementation. Quality appraisal is addressed through procedures to ensure systematic and rigorous attention to analysis and reporting.

### Data Management

Each investigator will document subject data in his/her own subject files. These subject files will serve as source data for the study. Data collected during this study as recorded on the appropriate source documents will be entered in a web-based electronic data capture (EDC) system specifically developed for the study and provided by the clinical research organisation (CRO) and project partner, Mediolanum Cardio Research (MCR), Milano, Italy. The e-CRFs will be reviewed periodically for completeness, consistency, and query status by the data management personnel of the CRO. Remote monitoring will be regularly performed by the CRO staff in order to oversee the progress of the study, completion, and quality of collected data. The raw sensor data, collected with the PDMonitor devices, and its processed data are uploaded and pseudonymized stored at the PD Neurotechnology's cloud platform.

### Harms

All adverse events, adverse reactions, and serious adverse events or reactions that occurred from the signature of the informed consent during the whole study duration will be recorded in the specific section of the e-CRF. Death events due to disease progression will not be considered as serious adverse event (SAE); however, data will also be recorded in a specific section of eCRF. Adverse events will be collected and coded using the most current version of the Medical Dictionary for Regulatory Activities (MedDRA). Each adverse event will be categorized by severity (mild, moderate, severe) and seriousness (serious, non-serious). The investigator will follow up the outcome of any Adverse Events (clinical signs, laboratory values or other, etc.) until the return to normal or consolidation of the patient's condition. In the case of any Serious Adverse Event, the patient will be followed up until clinical recovery is complete and laboratory results have returned to normal, or until progression has been stabilized.

## Discussion

The awareness of the possible merits of palliative care interventions for people with PD is growing (14, 64). However, we still do not fully understand how to optimally design palliative care models, and little is known about its potential impact for this patient population (13). In 2020, two large randomized controlled trials published the effects of multidisciplinary palliative care teams, with inconsistent results. The first one, conducted in American outpatient clinics, evaluated a multidisciplinary palliative care model for PD patients and their family caregivers. The patients received palliative care support in person or by telemedicine sessions, every 3 months for 12 months. The study showed a modest, but significant improvement in patients' quality of life after 6 months, leaving caregiver burden unchanged. In addition, non-motor symptom burden, motor symptom severity, completion of advance directives, caregiver anxiety, and caregiver burden favoured the intervention group at 12 months (24). The second study targeted people with long-term neurological conditions, including PD. This UK-based study evaluated a short-term palliative care intervention, using a comprehensive assessment, personalized care planning, case management, and care coordination, and advising existing care providers. The intervention lasted 6–8 weeks, with three distinct sessions for the patient and family caregiver with the multi-professional palliative care teams. After 12 weeks, no change in eight key palliative care symptoms emerged, although the intervention was associated with lower healthcare costs (65).

The PD_Pal intervention takes a different approach: instead of involvement of a multidisciplinary care team, we will assign a dedicated nurse, who will act as the personal case manager for the patient and family caregiver. The nurse will lead the conversations, create a relationship based on mutual trust, and involve other disciplines whenever needed. We deliberately opted for an intervention strategy, which combines specific training of a nurse in relevant areas of knowledge and skills with a prolonged in-depth support intervention for the patients and FCs. Throughout the intervention period, the nurses will join monthly digital meetings to share their experiences and discuss encountered problems and solutions. The Parkinson Support workbook is designed as a strategy to increase active engagement of patients and FCs in the ACP conversations about the future. Furthermore, the intervention is patient-centred and the patients will be deciding what will be discussed and when. None of the (sub)steps within the intervention are obligatory and patients can also add certain care (coordination) issues that are not included in the Parkinson Support Plan. To summarize, the PD_Pal model is advocating active engagement of patients as a key element for effective palliative care interventions (66).

The COVID-19 pandemic has affected the execution of the trial, which was planned to start in February 2020. The pandemic shows the importance of discussing goals of care, and to revisit or establish advance care plans in an early phase of the disease. Furthermore, the pandemic forced us to deploy telehealth solutions for e-consent, e-scales, and e-delivery of the intervention. The original protocol already included an option for teleconsultations for the PD_Pal nurses, as a measure to be inclusive for those patients who would live too far away from the clinical site for regular face-to-face visits. Now we anticipate to use a teleconsultation model as a necessary alternative, leveraging on earlier experiences. A review of 71 studies (67) concluded that, on the positive side, patients generally experience more comfort and control at home, leading to an exclusive digital connectedness between conversation partners. In contrast, professionals can experience reservations about addressing painful truths and emotional topics during teleconsultations as they did not feel sufficiently close. We will therefore strive for a first face-to-face contact between the PD_Pal nurse and the patient, before a teleconsultation solution will be applied. Nevertheless, the pandemic creates a unique opportunity to learn important lessons about the application of telehealth solutions in clinical research.

To conclude, studying the impact and feasibility of the intervention in seven European countries, each with their own cultural and organisational characteristics, will create a substantial body of knowledge about the future of palliative care for people with PD and their family caregivers.

## Ethical Considerations and Dissemination

The PD_Pal study design has been developed following the indications contained in the Charter of Fundamental Rights of the European Union. Informed consent will be obtained by each participant as in the Declaration of Helsinki (2013) and in line with ethic committee approval of the protocol. None of the steps within the intervention are obligatory. Patients can indicate they do (not yet) want to discuss or think about certain topics. All participants will be able to withdraw their informed consent to parts or to the overall participation at any point in time. When participants develop cognitive deficits, together with the FC, we will evaluate their ability and willingness to continue participating in the study.

The project results will be disseminated through the MDS Task Force on Palliative Care, the European Association for Palliative Care, the European Academy of Neurology, and the European Parkinson's disease association. In addition, dissemination will be accomplished through scientific publication on national and international journals as well as through participation to scientific and communication events related to the study topics. It is also important that the progress and findings are presented to PD patients and caregivers (usually in regional audiences) and by publishing lay summaries. PD_Pal will support the open-access (OA) initiative. OA literature is digital, online, free of charge, and free of most copyright and licensing restrictions. OA to research articles both in journals (“gold OA”) and in repositories (“green OA”) is foreseen.

## Ethics Statement

The studies involving human participants were reviewed and approved by the local ethics committees of all participating study sites (UK: London—Central Research Ethics Committee, REC reference 20/LO/0122, IRAS project ID 271717; Sweden: Etikprövningsmyndigheten, registration number 2020-00032; Austria: Ethikkommission für das Bundesland Salzburg, registration number 1117/2020; Greece: Scientific Council of the University Hospital of Ioannina, Protocol Nr 586/6-8-2020; Germany: Ethics Committee Philipps-University Marburg; study file number 163/19; Italy: Comitato Etico per la Sperimentazione Clinica della Provincia di Padova, protocol number CESC 4840/AO/20; Estonia: Reserach Ethics Committee of the University of Tartu (UT REC), protocols 2971T-16 and 327/M-16). The patients/participants provided their written informed consent to participate in this study.
